### Data collection

Data will be collected prospectively at predefined study time points. Assessments will occur at baseline, during each dose adjustment visit, throughout the maintenance phase, and following cessation of medication at 1 week and at 1, 3, 6, 12, 18, and 24 months, as outlined in Fig. 1.

At baseline, demographic data, medical history, current medications, and relevant clinical characteristics will be recorded. Baseline clinical assessments will include body weight, cardiovascular parameters (including ECG, echocardiogram, blood pressure and heart rate), and screening for possible undiagnosed depressive disorders.

During treatment and follow-up visits, body weight and cardiovascular parameters will be measured and recorded. Any adverse events, including cardiovascular events, will be documented throughout the study period. While participants are receiving the study medication, mood, cognition, and physiological responses will be assessed using the Amphetamine Interview Rating Scale (AIRS).

All data will be collected during routine general practice consultations by the treating clinician or trained study personnel and recorded in a secure electronic study database. Data completeness and accuracy will be monitored regularly, and any discrepancies will be reviewed and resolved where possible.

Participant information will be de-identified prior to analysis and stored securely in accordance with institutional data governance and privacy regulations.

### Data analysis

The primary analysis will adopt an intention-to-treat approach to ensure that all randomised participants are included in the evaluation, regardless of adherence to the treatment protocol. The primary outcome, the change in weight from baseline to both 6 months and 2 years, will be assessed using simple and multiple linear regression, adjusting for prespecified covariates such as age, sex, baseline BMI, and comorbidities. Secondary outcomes, including cardiovascular parameters, mood and cognition (AIRS scores), and feasibility metrics, will be analysed using appropriate regression models or repeated-measures mixed-effects models for longitudinal data. Missing data will be addressed primarily using available data under intention to treat; where missingness exceeds 10–15%, multiple imputation and complete-case analyses will be conducted as sensitivity analyses. Exploratory subgroup analyses by sex, baseline BMI, or baseline depressive status may also be performed. Adverse events will be summarised descriptively by type, severity, and relationship to treatment, with serious events reported individually.

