### Sample size

Sample size and power calculations for the primary analysis are centered on the expected weight loss at the 6-month endpoint. Based on the findings from Winslow et al., which indicated a significant weight reduction of 6.5 kg (95% CI: −10.0, −3.0) between treatment groups following 6 months of phentermine/topiramate therapy, we have designed our study to detect a similar effect [4]. To ensure adequate statistical power, we plan to recruit a total of 58 participants, with 29 assigned to each treatment arm. This sample size accounts for a projected attrition rate of 30% at 6 months, as observed in Poulton et al. [5]

The sample size calculation was based on 6-month outcomes, and that analyses at 2 years should be interpreted as exploratory and hypothesis-generating.

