### Randomisation and blinding

Participants will be randomised to receive either immediate-release DEX tablets or a placebo, following a pre-determined randomisation sequence generated by a computer system. The allocation ratio will be 1:1, using a block size of 4. The DEX and placebo tablets will be identical in appearance and dispensed in containers that conceal the treatment allocation. Participants and investigators will remain blinded throughout the study. Unblinding will only occur if clinically necessary, such as in cases of severe adverse reactions or medical emergencies where knowledge of the treatment allocation is essential for patient safety. Blinding efficacy will be assessed at the end of the intervention using the Bang Blinding Index (BBI) for both participants and investigators to evaluate the success of treatment allocation concealment.

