### Optimising attendance and handling missing data

To minimise missed follow-up assessments, all participants will be contacted ahead of their scheduled visits to confirm their attendance. If necessary, assessments can be postponed or rescheduled, with appropriate documentation maintained. Attendance at assessments during the dose titration phase is mandatory before considering any dose increases. Additionally, we will strive to collect follow-up data from participants who are unable to attend appointments during the maintenance dose phase or after treatment cessation by telephone. Participants will be asked to provide measurements taken from personal weight and blood pressure measuring equipment.

While we are committed to optimising adherence, some missing data are anticipated. To address this, we will compare baseline characteristics between participants with and without assessments at 6 and 24 months to identify potential biases in our final analysis. We will also investigate the reasons for study dropouts to better understand the mechanisms behind missing data, including any adherence issues related to the study protocol. Data will be reviewed regularly to identify missing or inconsistent entries, and where possible, clarification will be sought from the treating clinician or study records.

For the primary analysis, available data will be analysed using appropriate statistical methods depending on the extent and pattern of missingness. If the proportion of missing data is low, analyses will be conducted using complete case analysis. If missing data are substantial, appropriate statistical techniques such as multiple imputation will be considered to reduce potential bias.

Sensitivity analyses may be conducted to assess the impact of missing data on the primary outcome.

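### The primary analysis of 6-month weight change is in effect complete-case although described as including everyone randomised, and two sections give multiple imputation and complete-case analysis conflicting roles

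*Protocol article*

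**What the plan says.** Two sections of the protocol article set out how missing weights are handled.

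- **Data analysis.** The primary analysis is intention-to-treat, "to ensure that all randomised participants are included in the evaluation, regardless of adherence to the treatment protocol". Change in weight to 6 months and to 2 years is analysed by simple and multiple linear regression, with missing data dealt with primarily through the available data. Then: "where missingness exceeds 10–15%, multiple imputation and complete-case analyses will be conducted as sensitivity analyses". Repeated-measures mixed models are named for secondary outcomes only.
- **Optimising attendance and handling missing data.** For the primary analysis, the method depends on how much is missing and in what pattern. If little is missing, it is complete-case. Otherwise: "If missing data are substantial, appropriate statistical techniques such as multiple imputation will be considered to reduce potential bias". Sensitivity analyses are optional here.

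The Sample size section gives the expected scale: "we plan to recruit a total of 58 participants, with 29 assigned to each treatment arm", and "This sample size accounts for a projected attrition rate of 30% at 6 months".

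Under Design overview and Table 1, weight is recorded at weekly visits during the 6-week titration and at monthly visits after that.

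**The concern.** There are two linked problems.

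First, a regression on a change score at one time point can use only participants who have a weight at that time point. The promise to include everyone randomised and the stated method are therefore incompatible unless missing values are imputed, and in Data analysis imputation is only a sensitivity analysis.

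Second, the two sections assign the same two methods to different roles. Two analysts, each following one section faithfully, could report different primary results from the same data. The switch between methods is governed by a range in one section and by undefined adjectives in the other.

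What is at stake is the estimate of the primary outcome in a small trial. Dropout in a placebo-controlled weight-loss trial may well be related to weight response, to adverse effects, or to both. Where it differs between arms, a complete-case comparison can be biased, and the weekly and monthly weights that could reduce the bias go unused.

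**Working it through.** **1. The article's sample size.** It states 58 in total, 30% attrition and a target difference of 6.5 kg, but no significance level, power or SD, so 58 cannot be strictly reproduced. Assuming two-sided 5%, 80% power and an SD of 7.25 kg:

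- n per arm = 2 × (1.960 + 0.842)² × 7.25² / 6.5² = 19.5, rounded up to 20
- 20 / (1 − 0.30) = 28.6, rounded up to 29 per arm, or 58 in total

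On these assumptions the figure is consistent with a design that expects to analyse about 20 completers per arm.

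**2. Who remains in the available-data regression.**

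- Without a 6-month weight: 58 × 0.30 = 17.4
- Remaining: 58 − 17.4 = 40.6, about 41 (29 × 0.70 = 20.3 per arm)

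**3. Which branch is expected.**

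- 10% of 58 = 5.8 and 15% of 58 = 8.7, so the trigger corresponds to 6 to 9 participants.
- If each participant is missing independently with probability 0.30, P(6 or more missing) = 0.9999 and P(9 or more missing) = 0.997.

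The branch in which the two sections disagree is therefore the one the article itself expects.

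**4. The sections side by side.**

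| | Data analysis | Optimising attendance and handling missing data |
|---|---|---|
| Primary method | Regression on available data | Depends on extent and pattern of missingness |
| Complete-case | Sensitivity, above the trigger | Primary, if little is missing |
| Multiple imputation | Sensitivity, above the trigger | Considered for the primary analysis, if much is missing |
| Trigger | A range, 10–15% | No figure |
| Sensitivity analyses | Will be done above the trigger | May be done |

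**5. Possible size of bias.** Let d be the proportion lost in an arm, and g the amount by which that arm's dropouts lose less weight than its completers. Then

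all-randomised difference = completer difference − d(active) × g(active) + d(placebo) × g(placebo)

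Take a completer difference of 6.5 kg and d = 0.30 in each arm. The values of g are assumptions.

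| g (kg) | Active arm only | Placebo arm only | Same g in both arms |
|---|---|---|---|
| 2 | 6.5 − 0.6 = 5.9 | 6.5 + 0.6 = 7.1 | 6.5 |
| 4 | 6.5 − 1.2 = 5.3 | 6.5 + 1.2 = 7.7 | 6.5 |
| 6.5 | 6.5 − 1.95 = 4.55 | 6.5 + 1.95 = 8.45 | 6.5 |

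Complete-case is thus off by 0.6 to 1.95 kg, too large in the first column and too small in the second, and unbiased in the third.

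Simulations point the same way. They assumed a true difference of −6.5 kg, SD 8.4 kg (the SD of weight change in the article's 14-person pilot), correlation 0.9 per monthly lag, and dropout odds 1.28 to 2.12 times higher per 5 kg poorer last weight.

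- Weight-related dropout in placebo only, at 30%: complete-case estimates of −5.9 to −4.8 kg, or −5.6 to −4.4 kg with a linear mean trajectory.
- Weight-related dropout in active only: −7.4 to −8.5 kg.
- Same slope in both arms, 30% lost in each: −6.4 to −6.25 kg, a bias of 0.1 to 0.25 kg.
- Identical dropout coefficients in both arms, so that the proportion lost can differ: −6.3 to −5.8 kg, a bias of 0.2 to 0.7 kg.

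**The case against.** The best defence is that the article already does much of what is needed. Data analysis commits to multiple imputation above 10–15%, and at 30% both ends of that range are exceeded, so an imputed result would be reported in any case. The article also plans to compare the baseline characteristics of those with and without assessments, to investigate reasons for dropout, and to reschedule visits or collect data by telephone. All of this stands. It limits the harm, but it does not say which result is primary.

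A reader might infer more than the text supports on four points.

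- *That 30% of participants will be discarded.* The 30% is a projection, and telephone follow-up may lower it. The full loss also follows only if Data analysis governs, because under the other section imputation might become primary.
- *That the method will be chosen after seeing results.* The choice is tied to missingness, not to outcomes or treatment effects, and participants and investigators stay blinded. This is loose prespecification, not selection on results.
- *That the estimate is biased by a known amount or in a known direction.* It is not, as the sign changes and near-zero cases above show.
- *That home-scale weights bias the outcome.* The article says "Participants will be asked to provide measurements taken from personal weight and blood pressure measuring equipment", but this is a fallback that reduces missingness, and nothing in the document shows that it favours an arm.

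Using mixed models for secondary outcomes only is not an error in itself. A mixed model is also not the only valid remedy: multiple imputation using the interim weights recovers similar information.

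**Conclusion.** The concern holds as a stated contradiction about the primary result. It is not a detail left to an analysis plan, because the article fixes the handling twice and inconsistently. On the article's own projection, the primary regression would rest on about 41 of 58 participants while being described as including all of them, and the complete-case sensitivity analysis would add little to it.

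The consequence for the estimate is uncertain. Roughly 0.6 to 2 kg in either direction, against a target difference of 6.5 kg, requires weight-related dropout in one arm only. Bias is near zero if both arms lose the same proportion with the same relation to weight. These sizes rest on assumed mechanisms, and the counts rest on the projected 30%. Because neither the direction nor the size can be known beforehand, the method needs to be fixed in advance.

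**What to change.** Reconcile the two sections into one prespecified primary method:

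- It applies whatever the missingness. Delete both the 10–15% trigger and the undefined low/substantial rule.
- It uses all weights collected up to month 6, regardless of adherence. Restricting it to on-treatment weights would contradict the intention-to-treat statement. One suitable form is a mixed model for repeated measures with treatment, visit, treatment-by-visit and baseline weight, reporting the month-6 contrast. Multiple imputation using the interim weights is an acceptable alternative.
- A delta-adjusted or reference-based imputation is the fixed sensitivity analysis. Complete-case is supportive only.
- The text states that participants with no post-baseline weight enter only through imputation, so that the claim about all randomised participants is accurate.

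The cost is revised wording in two sections and a little more programming, with no new data. The downside is that the primary analysis would rely on a missing-at-random assumption, and the fixed sensitivity analysis is there to test it.

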### Protocol validation

Poulton et al., treated 14 people with obesity with DEX for 6 months [5]. There was a mean weight loss of 10.6 ± 8.4 kg, (P < 0.001), with 7 participants (50%) losing >10% of their total body weight. Six months post DEX treatment, weight regain reduced the mean weight loss to 7.0 ± 10.6 kg (p = 0.035). However, 3 participants still recorded a weight reduction of >10% and 4–5 participants recorded a weight reduction between 5–10% of their baseline body weight. Other important clinical outcomes identified a reduction in the severity of obstructive sleep apnoea in one participant, a decrease in the amount of insulin required for diabetes control in another and a reduction in the number of antihypertensive medications in a third participant.

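### For the 6-month weight, the two named missing-data sensitivity analyses do not, in standard form, test the assumption that the primary analysis rests on

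*Protocol article*

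**What the plan says.** All from the protocol article.

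- **Target (Data analysis).** The approach is intention-to-treat, so that "all randomised participants are included in the evaluation, regardless of adherence to the treatment protocol".
- **Model (Data analysis).** Change in weight to 6 months and to 2 years "will be assessed using simple and multiple linear regression, adjusting for prespecified covariates such as age, sex, baseline BMI, and comorbidities".
- **Primary handling of missing weights (Data analysis).** "Missing data will be addressed primarily using available data under intention to treat".
- **Sensitivity analyses (Data analysis).** Above 10–15% missingness, "multiple imputation and complete-case analyses will be conducted as sensitivity analyses". No imputation model is given.
- **Optimising attendance and handling missing data.** If much is missing, "appropriate statistical techniques such as multiple imputation will be considered to reduce potential bias". Further sensitivity analyses are optional and of unstated type. The section also plans a baseline comparison of those with and without assessments, a review of reasons for drop-out, and telephone collection of home weights for missed maintenance or post-treatment visits.
- **Sample size.** 29 per arm, a target difference of 6.5 kg, and a "projected attrition rate of 30% at 6 months".
- **Indications for early withdrawal.** A serious event judged related to the intervention leads to withdrawal from the study as a whole.
- **Protocol validation.** In the 14-person pilot, mean loss was 10.6 kg (SD 8.4) after six months of DEX. Six months after stopping, "weight regain reduced the mean weight loss" to 7.0 kg.

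**The concern.** A sensitivity analysis is useful when it changes the assumption that the primary result depends on. Here the primary depends on drop-outs having weight changes like those of comparable people who stayed. Complete-case analysis uses the same people as the primary. Standard multiple imputation fits its model to observed weights and carries that relationship over to the missing ones.

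Many DEX participants who leave will probably have stopped the tablets, and the pilot shows weight returning after DEX stops. The target effect counts those people too. If they do worse than comparable stayers, the primary and both named checks can share the same overstatement. Their close agreement could then be taken as support for a result whose main assumption had not been tested.

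**Working it through.** **Is the trigger expected to be met?** Projected attrition of 30% exceeds 10–15%. In 29 per arm that is 29 × 0.30 = 8.7 missing, leaving about 20.3 observed.

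**Does complete-case analysis add anything?** In a linear regression of a single change score, a participant without a 6-month weight contributes no outcome. The available-data fit and the complete-case fit therefore use essentially the same people. They differ only where covariates are missing.

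**How large could the overstatement be?** Let θ be the effect in stayers, p the share missing in each arm, and g_D and g_P the amounts (kg) by which drop-outs do worse than stayers on DEX and on placebo.

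All-randomised effect = θ − p(g_D − g_P)

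Inputs: θ = 6.5 kg (the target difference, assumed here to hold in stayers), p = 0.30 (Sample size) and g_P = 0 (assumed). The documents do not give g_D. Pilot regain is 10.6 − 7.0 = 3.6 kg, and 3.6/10.6 = 34% of the loss.

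| Assumption for DEX drop-outs | g_D (kg) | Overstatement (kg) | All-randomised effect (kg) |
|---|---|---|---|
| Lose the pilot's proportion of the effect | 0.34 × 6.5 = 2.2 | 0.30 × 2.2 = 0.66 | 5.84 |
| Regain the pilot's 3.6 kg | 3.6 | 0.30 × 3.6 = 1.08 | 5.42 |
| Look like placebo (extreme) | 6.5 | 0.30 × 6.5 = 1.95 | 4.55 |

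As a share of the all-randomised effect these are 0.66/5.84 = 11%, 1.08/5.42 = 20% and 1.95/4.55 = 43%.

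**Would imputation show it?** A large-sample simulation used the extreme case: 2,000 per arm, 30% drop-out in both arms, a 6.5 kg effect in stayers, and DEX drop-outs returning to placebo level.

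| Analysis | Estimated difference (kg) |
|---|---|
| All randomised, nothing missing | −4.7 |
| Complete case | −6.6 |
| Imputation by arm, no post-baseline weight | −6.6 |
| Imputation with an interim weight taken on drug | −6.6 |
| Imputation with an interim weight already showing the regain | −5.6 |

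Complete-case analysis and the first two forms of imputation agree with each other and miss the gap. The last form recovers about half of it. So the outcome turns on which weights enter the imputation model, and the article does not fix that.

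**The case against.** The strongest reply is that the article says only multiple imputation, without a model. Reference-based imputation is itself a form of multiple imputation, and a statistical analysis plan, not shown here, could specify it. The protocol also schedules interim weights and seeks home weights by telephone. In a further simulation of the extreme case, one interim weight already reflected stopping and was strongly related to the final weight (assumed correlation 0.8). Imputation then gave −4.92 kg against a true −4.55 kg, and complete-case analysis gave −6.50 kg. A reader might infer that neither named analysis could ever reveal an overstated effect. The documents do not support that.

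A reader might also infer that the pilot contradicts the assumption. It does not. It followed people after a six-month course and reports no weights for those who left during treatment. About two-thirds of the loss remained six months later (7.0/10.6 = 66%), which argues against total loss of benefit as the main scenario.

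Size is a fair objection too. In a simulation with 29 per arm, SD 8.4 kg and the pilot's proportional regain, 95% intervals kept about nominal coverage (0.947 for complete case, 0.950 for imputation), because the estimate's standard deviation is about 2.5 kg. If placebo drop-outs also do worse than placebo stayers, the bias shrinks.

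What remains is that the article commits to a named pair. One member essentially repeats the primary. The other helps only if built on off-drug weights, and nothing requires that. Telephone weights are described for missed visits in maintenance or after cessation; nothing says they extend to people withdrawn from the study or lost during titration. The baseline comparison and the review of reasons do not change the estimate.

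**Conclusion.** The point holds for the 6-month weight in this limited form: as named, and in their standard form, the two sensitivity analyses do not test whether drop-outs do worse than comparable stayers. The plausible overstatement is 0.7–1.1 kg on a 6.5 kg effect, with 1.95 kg as an extreme.

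These figures assume 30% drop-out in the DEX arm, a 6.5 kg effect in stayers, placebo drop-outs who resemble placebo stayers, and pilot regain as a rough guide to people whom the pilot did not measure. The 43% relative overstatement should not be read as the expected size, since it needs DEX drop-outs to look exactly like placebo.

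A reader might extend the argument to the 2-year outcome, because the same sentence covers both time points. It does not carry over: by then everyone is off drug, so the contrast between on-drug stayers and off-drug drop-outs is weak. The differing roles given to imputation in the two sections are a separate matter, and settling them would not resolve this one.

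This is a worthwhile, inexpensive improvement to a stated method. It does not invalidate the primary analysis.

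**What to change.** In Data analysis, and consistently in Optimising attendance and handling missing data:

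1. Replace complete-case analysis as a sensitivity analysis of 6-month weight with one or both of the following:
   - **Delta-adjusted tipping point.** Add increasing amounts (1, 2, 3 … kg) to the imputed DEX weights until the 95% interval for the difference includes zero, and report that amount. At 30% missing, each added kilogram moves the estimate by about 0.30 kg, so the result can be read against the pilot's 3.6 kg.
   - **Reference-based multiple imputation.** Impute missing DEX weights from the placebo-arm model, given baseline and earlier weights, and missing placebo weights from their own arm.
2. State that the multiple imputation model uses interim weights and any weights obtained after discontinuation or by telephone.
3. Report these results beside the primary estimate.

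The cost is a few sentences and a little more analysis, with no new data, visits or participants. The reference-based estimate will probably be smaller than the headline figure, so the choice should be fixed before unblinding.
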